## Abstract

**Background:**

The application of 38 % silver diamine fluoride (SDF) has been shown to be effective in arresting early childhood caries (ECC). Since SDF is not available in certain countries, some dentists use adjunctive application of 25 % silver nitrate (AgNO_3_) and 5 % sodium fluoride (NaF) to arrest ECC. This randomised controlled trial will systematically compare the efficacy of a 25 % AgNO_3_ solution followed by 5 % NaF varnish with that of a 38 % SDF solution in arresting ECC when applied at half-yearly intervals over a 30-month period.

**Methods/Design:**

This study is a randomised, double-blinded, non-inferiority clinical trial. The hypothesis tested is that adjunctive application of 25 % AgNO_3_ followed by 5 % NaF is at least not appreciably worse than a 38 % SDF in arresting ECC. Approximately 3100 kindergarten children aged 3–4 years will be screened and at least 1070 children with caries will be recruited. This sample size is sufficient for an appropriate statistical analysis (power at 90 % (*β* = 0.10) with a 2-sided type-I error of *α* = 0.05), allowing for an overall 20 % drop-out rate. The children will be randomly allocated into 2 groups to treat their caries over a 30-month period:Group A – biannual adjunctive application of a 25 % AgNO_3_ solution and a 5 % NaF varnish, andGroup B – biannual adjunctive application of a 38 % SDF solution followed by a placebo varnish.

Clinical examinations will be conducted at 6-month intervals. Primary outcome measured is the number of active caries surfaces which are arrested. Information on confounding factors such as oral hygiene habits will be collected through a parental questionnaire.

**Discussion:**

We expect that adjunctive application of 25 % AgNO_3_ solution and 5 % NaF varnish and of 38 % SDF solution can both effectively arrest ECC. Lower concentrations of silver and fluoride are contained in 25 % AgNO_3_ and 5 % NaF, respectively, than in 38 % SDF; therefore, AgNO_3_/NaF are more favourable for use in young children. Because its use for caries management is painless, simple, low-cost, and approved in many countries, AgNO_3_/NaF could be widely recommended and promoted as an alternative treatment to conventional invasive management of ECC.

**Trial registration:**

ClinicalTrials.gov: NCT02019160. Date of registration: 11 December 2013.

**Electronic supplementary material:**

The online version of this article (doi:10.1186/s13063-015-0960-2) contains supplementary material, which is available to authorized users.

## Background

### Early childhood caries

Early childhood caries (ECC) is defined as the presence of one or more decayed, missing (due to dental caries), or filled tooth surfaces in the primary teeth of a child of 71 months of age or under [1]. Despite advances in clinical care and dental research, ECC remains a challenging problem. The United States (US) Centers for Disease Control and Prevention has reported that 28 % of all US toddlers and preschoolers are affected by ECC and that nearly half of US children have ECC before entering kindergarten [2]. ECC cause pain and infection, and advanced caries will progress into the tooth pulp to eventually form a dental abscess [3]. If cases remain untreated they lead to tooth loss, which affects dentition. Poor dentition significantly affects children’s nutrition and consequently their growth, development, and general health. Socially disadvantaged children, such as those from poor families and those whose parents have low educational levels, are disproportionately affected [4, 5]. The FDI World Dental Federation *Oral Health Atlas* reported that millions of children are suffering from untreated ECC; however, with its great shortage of community dentists, the present dental care delivery system cannot cope with this high ECC prevalence [6]. Moreover, prevailing restorative methods for preventing and treating ECC are neither available nor affordable to children from disadvantaged families, who exhibit a particularly high caries risk [7]. Although there have been efforts to treat ECC in developing areas (e.g., using mobile dental clinics with portable equipment), in most cases the technology has proven to be too complicated for sustained use [8]. The cost of basic sets of instruments, dental materials and infection-control products is also too high. In this situation, a new approach for managing ECC is needed. This study uses a non-operative strategy for caries management in preschool children.

**Fig. 1 Fig1:**
[figure not shown]
Flow diagram of the clinical trial

### Silver diamine fluoride

Fluoride was introduced to prevent caries more than 50 years ago [9]. Clinical studies have demonstrated that using 38 % silver diamine fluoride (SDF) can prevent and arrest ECC [10–15]. A literature review of SDF suggested that 38 % SDF can be an effective agent in preventing new caries and arresting dental caries in the primary teeth of children [16]. Another review concluded that SDF is an effective, efficient, and equitable caries-control agent [17]. Milgrom and Chi [18] advocated SDF therapy as an important prevention-centred caries management strategy during critical early childhood periods. The clinical trial by dos Santos et al. [19] concluded that 38 % SDF was better than interim restorative treatment with a glass ionomer for arresting ECC. Nevertheless, 38 % SDF exhibits a high fluoride concentration (44,800 ppm), which has concerned some researchers because of the possible onset of dental fluorosis [20]. Although SDF is used in countries in Asia and South America, SDF has not yet been approved for use in many European countries or in the USA [21].

### Adjunctive application of silver nitrate solution and sodium fluoride varnish

Although dental fluorosis can develop with increased fluoride dosage, fluoride use under professional instruction is generally safe and effective even in young children [9]. Sodium fluoride (NaF) varnish at 5 % contains 22,600 ppm of fluoride ions and is a common professionally applied topical agent in caries management. A literature review on the use of NaF varnish in managing ECC in children found that fluoride varnish appears to be the easier caries prevention method for both the dentist and the child [22]. However, NaF varnish is not effective in arresting dentine caries [10, 13]. Duffin [23] proposed using silver and fluoride ions from 25 % silver nitrate (AgNO_3_) solution followed by 5 % NaF varnish to arrest caries. A solution of 25 % AgNO_3_ and 5 % NaF varnish are accepted by most countries and their corresponding authorities such as the US Food and Drug Administration [23]. One laboratory study has suggested that 25 % AgNO_3_ solution and 5 % NaF varnish may be as effective as 38 % SDF in arresting dentine caries [24, 25]. However, a discussion of the use of AgNO_3_ and NaF by the Oregon Dental Association concluded that more research demonstrating efficacy and safety is required to meet the standard for evidence-based dentistry [21]. A literature search on PubMed on 1 December 2014, however, found that no research group has thus far published a well-designed study on the effectiveness of AgNO_3_ and NaF in the control of ECC.

### Objective

The overall objective of the randomised controlled trial is to systematically compare the effectiveness of a 25 % AgNO_3_ solution followed by 5 % NaF varnish with that of a 38 % SDF solution in arresting caries teeth among preschool children when applied at half-yearly intervals over a 30-month period.

### Hypothesis

In this non-inferiority randomised controlled trial, the hypothesis tested is that the biannual topical application of 25 % AgNO_3_ solution followed by 5 % NaF varnish is at least not appreciably worse than a 38 % SDF solution in terms of caries arrest in the primary teeth of preschool children.

## Methods/Design

### Trial design

This is a randomised, double-blind, non-inferiority clinical trial. The extension of the Consolidated Standards of Reporting Trials 2010 Statement will be followed [26]. The flowchart of this study is shown in Fig. 1.

### Setting

Kindergartens in Hong Kong who have joined our outreach dental service will be invited to join this study. Preschool children aged 3–4 years who have tooth decay and are attending the first year of kindergarten will be invited to join this study. An invitation letter will be sent to the parents explaining the purpose and procedures of this study. Written parental consent will be obtained before they are included in this clinical trial. We have trained an outreach team comprised of a dentist and a dental assistant to assess caries prevention and the caries-arresting effects of different treatments in preschool children in the kindergartens.

### Participants

The children included in the study should: a) be aged 3–4 years and are attending the first year of kindergarten, b) be generally healthy, c) have parental consent, and d) have at least 1 tooth with untreated caries with cavitation that extends into the dentine at baseline examination. Children who are uncooperative and difficult to manage, with severe forms of hypoplasia of fluorosis or other oral diseases, wearing orthodontic devices or under dental treatment, have major systemic diseases, or are on long-term medication will be excluded.

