### Clinical examination

A clinical examination of the participating children will be performed in the kindergarten, primarily through a careful visual inspection with the aid of a disposable World Health Organisation Community Periodontal Index (CPI) probe (405/WHO probe, Otto Leibinger, Mühlheim, Germany) and a front-surface dental mirror with light-emitting diode intra-oral illumination (MirrorLite, Kudos Crown Limited, Hong Kong, China). The oral hygiene status will be measured using the visible plaque index (VPI). The buccal and lingual surfaces of 6 index teeth (55, 51, 63, 71, 75, and 83) will be examined. The presence or absence of visible plaque on the caries surface will also be recorded.

The tooth status (decayed, missing, filled surfaces (dmfs) score), tooth discolouration, and hyper-mobility will be recorded. Teeth with a caries lesion extending into the pulp or signs suggesting that the teeth are non-vital, such as tooth discolouration, hyper-mobility or abscess, will not be included in this study.

The caries will be diagnosed at the cavitation level. The carious lesion will be gently explored with the CPI probe in the centre of the lesion. Great care will be taken to avoid tooth damage during the probing. A lesion will be recorded as active if softness is detected upon gentle probing. If the dentine surface is hard to probing, it will be classified as an arrested caries [11–13, 15, 27]. All surfaces (i.e., buccal, lingual, mesial, distal, and occlusal for posterior teeth) of each tooth will be assessed. Active caries at the baseline that become arrested in the follow-up examinations will be used as the main treatment outcome.

A designated experienced outreach dentist will be the examiner throughout the 30-month study. The intra-examiner agreement on the plaque and caries assessment will be monitored and conducted in 10 % of the children at each stage of the study.

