### Randomisation and treatment allocation

#### Allocation concealment

The participating children with caries will first be categorised as either: (1) having a high caries rate (or severe early childhood caries, as defined by the American Academy of Paediatric Dentistry [1]), which is defined as the presence of more than 3 untreated caries surfaces, or (2) having a low caries rate. The children will then be allocated by a stratified randomisation method using a computer-generated random-number table into the following 2 groups:Group A – biannual topical application of 25 % AgNO_3_ solution followed by 5 % NaF varnish; andGroup B – biannual topical application of 38 % SDF solution followed by a placebo varnish.

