### Outcome measure

The outcome measure (primary endpoint) is the number of soft (active) caries surfaces that become arrested (hardened) after 30 months. The outcome measure will be administered at baseline and at the 6-monthly follow-up examinations. Children and their parents have the right to receive dental treatment by other dentists. To our experience from previous clinical trials [11, 12], almost all participants will not be cared by other dental personnel, and we will include questions about the receipt of other dental treatment in baseline and follow-up interviews.

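### Inclusion criterion (d) does not require an active lesion, so a child with only hard cavities can be randomised and must score 0 on an endpoint that counts baseline-active surfaces only

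*Protocol article*

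**What the plan says.** Four parts of the protocol article bear on this.

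- **Participants, criterion (d).** A child must "have at least 1 tooth with untreated caries with cavitation that extends into the dentine at baseline examination". Lesion activity is not mentioned here or in the exclusions that follow.
- **Clinical examination.** Lesions are divided by probing: "A lesion will be recorded as active if softness is detected upon gentle probing", whereas "If the dentine surface is hard to probing, it will be classified as an arrested caries". Both kinds are called caries. The section also keeps some teeth out of the study: "Teeth with a caries lesion extending into the pulp or signs suggesting that the teeth are non-vital". That exclusion is written for teeth, and criterion (d) does not refer to it.
- **Outcome.** Clinical examination states: "Active caries at the baseline that become arrested in the follow-up examinations will be used as the main treatment outcome". Outcome measure gives the primary endpoint as "the number of soft (active) caries surfaces that become arrested (hardened) after 30 months".
- **Analysis.** Statistical methods specifies intention to treat. Subject-level analysis compares the mean count per child with a fixed margin of −0.5 surfaces. The conditional per-protocol set removes children who depart from the protocol, not children who had no active surface at baseline.

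**The concern.** Eligibility is defined on one set of lesions and the endpoint on a smaller one. A child with hard cavities only meets criterion (d), is randomised and stays in the intention-to-treat set, but has no surface that can change from soft to hard. The score is 0 by construction, whichever treatment is given.

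In a superiority trial such children would mainly cost power. In a non-inferiority trial with an absolute margin they also favour the conclusion sought. They pull the two means together while the margin does not move, so a treatment that is worse in children it could help looks closer to SDF than it is.

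**Working it through.** **1. Can such a child enter and stay in?** Criterion (d) needs untreated cavitated dentine caries, and the examination section classes a hard lesion as caries (arrested). The screening figure does not suggest a narrower meaning: it is 1070 / 0.35 = 3057.1, given as 3058, which treats every child with caries as recruitable. No section shown removes a child without an active surface. So the child enters, and scores 0.

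**2. Inputs.**
- From Sample size and power calculation: margin −0.5, SD 2.5, 856 evaluable children.
- From Statistical methods: one-sided level 0.025.
- Assumed: 1:1 allocation (428 per arm); mean μ = 2.5 and SD 2.5 among treatable children; f over a range, because the article gives none.

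**3. The plan's own figure.** 856 / 0.8 = 1070 reproduces. The 856 itself does not: margin 0.5, SD 2.5, 90 % power and one-sided 0.025 need 1052 in total, whereas one-sided 0.05 gives 858. At 428 per arm and one-sided 0.025 the power is 83.3 %. That is a separate matter. The 428 is used here only as the planned size.

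**4. Dilution model.** A share f scores 0 in both arms. With true difference δ among treatable children:
- observed difference = (1 − f) × δ
- variance per child = (1 − f) × 2.5² + f(1 − f) × μ²
- SE = √variance × √(2/428)
- P(non-inferiority declared) = Φ[((1 − f)δ + 0.5)/SE − 1.96]

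Worked case, f = 10 %, δ = −0.5: the difference is −0.45; the variance is 0.9 × 6.25 + 0.09 × 6.25 = 6.1875, so the SD is 2.487; SE = 2.487 × 0.06836 = 0.170; and Φ(0.05/0.170 − 1.96) = Φ(−1.666) = 0.048.

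| f | Observed difference | Declared non-inferior when δ = −0.5 | Deficit among treatable children that appears as −0.5, i.e. −0.5/(1 − f) |
|---|---|---|---|
| 0 | −0.500 | 2.5 % | −0.500 |
| 2 % | −0.490 | 2.9 % | −0.510 |
| 5 % | −0.475 | 3.5 % | −0.526 |
| 10 % | −0.450 | 4.8 % | −0.556 |
| 20 % | −0.400 | 8.6 % | −0.625 |

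**5. Sensitivity.** At f = 20 %, the rate runs from 9.2 % (μ = 1.5) to 8.0 % (μ = 3.5). If 2.5 is taken as the SD of the whole sample, it is 8.5 %. If δ = 0, the observed difference is 0 for every f, so there is no bias.

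**The case against.** **The margin is set on all recruited children.** This is the strongest objection, and it is correct. For the difference in means over everyone randomised, the one-sided error stays at 2.5 % whatever f is. A reader might infer from the table that the trial's stated test exceeds its nominal level, and the article does not support that. The inflation concerns the deficit among children who can respond, a group for which no separate margin is set. What remains is that the comparison of interest is between two treatments for active lesions, and children without such lesions carry no information about it.

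**The share f is unknown and may be trivial.** This also stands. What counts is the share of children with no soft surface in any included tooth, not the share of lesions that are hard. At 2 % the effect is negligible. A reader might assume a large f and conclude that the error is several times nominal, but nothing in the article supports any particular value.

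**Pulpally involved teeth are already dealt with.** Largely so. A reader might infer that children whose only lesions are in such teeth also enter and score 0. Since those teeth are kept out of the study, the natural reading is that they cannot qualify a child. The text only lacks an explicit link to criterion (d).

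**Stratification.** The high-caries stratum is defined by "which is defined as the presence of more than 3 untreated caries surfaces", without regard to activity. A reader might call this a fault as well. It is a permissible stratifier and no bias from it has been shown, so changing it is optional and not part of this point.

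**Conclusion.** The mismatch is real and follows from the text: criterion (d) admits a child with hard lesions only, and the endpoint gives that child 0 in either arm. If AgNO3/NaF is truly worse among treatable children, the effect is always towards non-inferiority. Its size depends on f, which the article does not give. A true deficit of 0.5 among treatable children would pass about 2.9 % of the time at f = 2 % and 8.6 % at f = 20 %, against 2.5 %. These figures assume 428 per arm, mean and SD 2.5 among treatable children, and a normal approximation. The point merits correction because the remedy is short and brings eligibility into line with the endpoint, not because a large bias has been demonstrated.

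**What to change.** 1. **Amend criterion (d)** to require at least one active (soft) cavitated dentine surface in a tooth that the Clinical examination section includes. The same sentence then makes explicit that a pulpally involved or non-vital tooth cannot qualify a child.

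2. **For children already enrolled** (Trial status gives recruitment from 15 September 2014), report the non-inferiority analysis restricted to those with at least one such surface at baseline, alongside the all-randomised analysis, and require the two conclusions to agree. Restriction does not break the randomised comparison. Activity is recorded at the baseline examination, before treatment, by an examiner unaware of allocation, and the stratified allocation itself needs the baseline caries count first.

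3. **Report f** from the baseline data, so that readers can see whether the issue mattered.

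**Cost.** Screening rises in proportion to 1/(1 − f): from 3058 to about 3120 at f = 2 % (3058/0.98), 3398 at 10 % (3058/0.90) and 3823 at 20 % (3058/0.80). The restricted analysis loses precision. At f = 20 % it keeps about 342 per arm (428 × 0.8), so SE = 2.5 × √(2/342) = 0.191 and power is Φ(0.5/0.191 − 1.96), about 74 %, against 83 % at 428 per arm. Requiring both analyses to agree cannot give more power than the restricted one. At small f these costs are slight.

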### Recruitment and screening

Oral health education will be provided to the children in the participating kindergartens, followed by a baseline oral examination. Potential participants will be recruited by trained field workers of the outreach team after the initial oral examination.

### Clinical examination

A clinical examination of the participating children will be performed in the kindergarten, primarily through a careful visual inspection with the aid of a disposable World Health Organisation Community Periodontal Index (CPI) probe (405/WHO probe, Otto Leibinger, Mühlheim, Germany) and a front-surface dental mirror with light-emitting diode intra-oral illumination (MirrorLite, Kudos Crown Limited, Hong Kong, China). The oral hygiene status will be measured using the visible plaque index (VPI). The buccal and lingual surfaces of 6 index teeth (55, 51, 63, 71, 75, and 83) will be examined. The presence or absence of visible plaque on the caries surface will also be recorded.

The tooth status (decayed, missing, filled surfaces (dmfs) score), tooth discolouration, and hyper-mobility will be recorded. Teeth with a caries lesion extending into the pulp or signs suggesting that the teeth are non-vital, such as tooth discolouration, hyper-mobility or abscess, will not be included in this study.

The caries will be diagnosed at the cavitation level. The carious lesion will be gently explored with the CPI probe in the centre of the lesion. Great care will be taken to avoid tooth damage during the probing. A lesion will be recorded as active if softness is detected upon gentle probing. If the dentine surface is hard to probing, it will be classified as an arrested caries [11–13, 15, 27]. All surfaces (i.e., buccal, lingual, mesial, distal, and occlusal for posterior teeth) of each tooth will be assessed. Active caries at the baseline that become arrested in the follow-up examinations will be used as the main treatment outcome.

A designated experienced outreach dentist will be the examiner throughout the 30-month study. The intra-examiner agreement on the plaque and caries assessment will be monitored and conducted in 10 % of the children at each stage of the study.

### Questionnaire survey

A validated parental questionnaire [4, 5] regarding their children’s oral hygiene habits (e.g., tooth-brushing and flossing), parent-assisted tooth-brushing, fluoride agent use (e.g., fluoride toothpaste and fluoride mouthwash), when brushing with fluoride toothpaste commenced, fluoride concentration in the used toothpaste, dental visit behaviour, snacking habits, parental educational level, family total income, and family status (single-parent or 2-parent households) will be administered at baseline and again at the 18-month and 30-month follow-up visits (Additional file 1). The questionnaires will also assess parental satisfaction with their child’s oral health and dental aesthetics. In the follow-up questionnaires, questions will also be asked about the potential post-treatment complications of the SDF application, such as pain in the treated tooth and gingival irritation around the treated tooth.

